##### Physical activity

Moderate‐to‐vigorous physical activity (MVPA [≥ 3 METs]) is recommended as part of multi‐component weight management interventions^19^ and also has numerous additional health benefits for adults with DS which include maintaining components of cognition, including attention, memory, and executive function.^7^, ^20^ Thus, promoting recommended levels of MVPA in the weight management intervention may potentially confound our results. However, given the potential health benefits of MVPA, we felt that it would be unethical to recommend that participants refrain from engaging in MVPA. We chose to recommend 150 min per week of MVPA following the Physical Activity Guidelines for Americans.^21^ We will not ask participants to set MVPA goals during interventionist meetings or to self‐monitor MVPA across the intervention for the proposed trial. Data from our previous trials in adults with ID which used the same 150 min per week MVPA recommendation in addition to participant MVPA goal setting during meetings with interventionists and continuous self‐monitored MVPA using a Fitbit were generally unsuccessful in increasing MVPA.^17^ Thus, we anticipate minimal increases in MVPA across the intervention in the weight loss arm. However, to control for any between‐arm differences in MVPA across the intervention, we will assess MVPA using portable accelerometers (see the Outcomes section) in both the weight loss and control arms at baseline 6 and 12 months.

##### Self‐monitoring

Participants will be asked but not required to monitor diet daily and body weight monthly over the 12‐month intervention. For this trial, participants with DS with assistance from their study partner will log food/beverages (meals/snacks) using the CoachCare platform by entering the food name and selecting the portion size, or by scanning the bar code of the food item using the iPad. A bar graph displays calories consumed compared with the goal, providing immediate feedback. Reminders will be sent via the app if no information is reported for a given meal. Participants will self‐weigh during monthly education/behavioral counseling video sessions using the wireless digital scale provided by the study which automatically syncs with the CoachCare app and updates a visual display of weight change. CoachCare platform data, which will be accessible in real time to interventionists, will be used *only* to provide motivation and feedback during the education/behavioral counseling sessions.

##### Education/behavioral counseling sessions

These sessions (∼45 min) will be conducted via a Health Insurance Portability and Accountability Act (HIPPA) compliant video conference meeting over Zoom with a trained interventionist, monthly across the 12‐month intervention. Education/behavioral counseling sessions will include a review of participants self‐monitored diet and weight data, individual problem‐solving and goal setting, and reviewing an interactive lesson on a weight management topic such as energy density (increase volume, not calories), the importance of fruits/vegetables, eating in social situations, basic cooking skills, and so forth. Participants and study partners will receive an automated text message and email bi‐weekly using the CoachCare app encouraging them to apply the topics discussed in the monthly lesson.

#### Control arm: General health education

2.5.2

##### Orientation

Similar to the weight loss arm, interventionists will conduct a 30 min visit with participants and study partners prior to initiating the intervention to provide an overall description of the health education curriculum and the meeting schedule. Participants will be provided with and receive a tutorial on the use of an iPad loaded with Zoom video conferencing software.

##### Education sessions

Education sessions (∼30 min) will be conducted via a HIPPA compliant Zoom meeting, monthly across the 12‐month intervention. Topics include injury prevention, oral health, sleep hygiene, hydration, exercise and physical activity, healthy eating, importance of health behaviors for disease prevention, and so forth. Sessions will provide information regarding these topics and will not ask participants to self‐monitor behaviors or make lifestyle changes relative to any of these topics. Participants and study partners will receive an automated text message and email bi‐weekly reviewing the previous month's topic.

### Intervention fidelity

2.6

Twenty percent of education sessions in both the weight loss and control arms will be video recorded and reviewed by study staff. The content delivered during each session will be compared with a checklist of scheduled content. Interventionists presenting < 80% of the scheduled content for any session will receive additional training and will be dismissed if the problem recurs.

### Outcome assessments

2.7

All assessments will be completed by appropriately trained staff blinded to the intervention arm (Table 3). All outcomes will be assessed during two separate visits to an academic medical center. Visit 1 will include assessments of height, weight and waist circumference, blood pressure, a blood draw for plasma biomarkers, cognitive function, diet intake, and skin carotenoid content. These assessments will require ∼ 120 min to complete. Visit 2, which is optional, will include neuroimaging and will require ∼ 60 min to complete. Staff will receive refresher training and complete reliability assessments for all physical measures two to three times per year.

**TABLE 3 alz70219-tbl-0003:** Outcome assessments across a 12‐month weight loss intervention in adults with Down syndrome.

Assessments	Pre‐study	Baseline	6 months	12 months
*Screening*				
DSQIDD	X			
Demographic health questionnaire	X			
Participant health history	X			
*Visit 1*				
Anthropometrics and blood pressure		X	X	X
Blood draw		X	X	X
3‐Day photo assisted food record		X	X	X
Skin carotenoid content		X	X	X
Kaufman Brief Intelligence Test (KBIT‐2)		X		
Modified Cued Recall task		X	X	X
Down Syndrome Mental Status Examination		X	X	X
Stroop dog and cat		X	X	X
NTG‐Early Detection Screen for Dementia (NTG‐EDSD)		X	X	X
Dementia questionnaire for people with learning disabilities (DLD)		X	X	X
Neuropsychiatric Inventory (NPI)		X	X	X
Vineland Adaptive Behavior Scales		X	X	X
Accelerometer		X	X	X
*Visit 2*				
MRI/MRS		X		X

Abbreviations: DSQIID, Dementia Screening Questionnaire for Individuals with Intellectual Disabilities; MRI, magnetic resonance imaging; MRS, magnetic resonance spectroscopy; NTG, National Task Group.

#### Visit 1: Clinical and cognitive assessment

2.7.1

##### Blood draw

We will collect a blood sample to analyze plasma biomarkers related to AD (Aβ42/40, pTau217, NfL, and GFAP) and cardiometabolic biomarkers (lipids, glucose, glycated hemoglobin [HbA1c], inflammatory markers). Phlebotomy will occur after an overnight fast (>8 h). AD biomarkers will be collected using ethylenediaminetetraacetic acid (EDTA) as an anticoagulant, inverted 8× to mix and processed at 1800 × *g* for 10 min at 4°C prior to storage at −80°C. Cardiometabolic biomarkers will be collected into gold top serum separator tubes, inverted 8× to mix, and allowed to clot for 30 min at room temperature prior to centrifugation at 1500 × *g* for 10 min prior to analysis. AD biomarker analyses will be performed on the first freeze‐thaw cycle using the Simoa HD‐X (Quanterix, Billerica, MA, USA). Cardiometabolic biomarkers will be analyzed in a clinical laboratory.

##### Anthropometrics

A clinician will measure weight, height, and waist circumference. Weight will be measured on a calibrated scale to the nearest 0.1 kg. Standing height will be measured with a stadiometer. BMI will be calculated as weight (kg)/height (m^2^). Waist circumference will be assessed using standard procedures such as those described by Lohman et al.^22^ Systolic and diastolic blood pressure will be assessed with two measurements using a calibrated automatic cuff on the left arm with the participant in a seated position.

##### Dietary intake

Dietary intake will be assessed using photo‐assisted food records^23^ over 3 consecutive days (2 week days/1 weekend day) starting the week prior to scheduled outcome assessments. Participants will be encouraged to take before and after photographs of all foods and beverages consumed using the iPad camera which automatically date and time stamps photos for easy identification. Hard copy records will be completed to account for details not discernible from photos (e.g., skim or whole milk). During outcome visits, staff will review photos and food records and clarify ambiguities. If no photo is available for a meal, food record data will be used.

##### Skin carotenoid content

Skin carotenoid content will be assessed by a finger scan using the Veggie Meter (Longevity Link Corporation), as a biomarker of fruit and vegetable intake.^24^

##### Cognitive assessment

A trained psychometrist will administer a psychometric battery to assess broad cognitive abilities using the Down Syndrome Mental Status Exam (DSMSE),^25^ modified Cued Recall Task,^26^ and The Modified Cats and Dogs Task.^27^ Additionally at baseline, we will collect the Kaufman Brief Intelligence Test Second Edition^28^ to measure premorbid ID level. These cognitive measures have been shown to be sensitive to early AD‐related cognitive decline^26^, ^29^ and are being used in national cohorts examining AD in DS^30^ which will allow for harmonization of data.

##### Study partner outcomes

Study partner‐based interviews will focus on participants’ adaptive, cognitive, neuropsychiatric status and possible observed AD symptomatology and will include the Dementia Questionnaire for People with Learning Disabilities (DLD),^31^ the National Task Group Early Detection Screen for Dementia (NTG‐EDSD),^25^ The Vineland Adaptive Behavior Scales, third edition (VABS‐3),^32^ and The Neuropsychiatric Inventory (NPI‐Q).^33^ These informant‐based cognitive measures are associated with early changes in plasma and imaging assessed biomarkers related to AD.^29^, ^34^, ^35^

##### Physical activity

Participants will be asked to wear an ActiGraph (ActiGraph GT9X, ArchiMed Co, Lyon, Auvergne‐Rhone‐Alpes, France) tri‐axial accelerometer (3.3 cm × 4.6 cm × 3.5 cm, wt. = 19 g., dynamic range ± 8 g) watch on the non‐dominant wrist for 7 consecutive days, including at night. ActiGraphs will be administered at the study visit and returned by postage paid mail following completion of all assessments.

#### Visit 2: Neuroimaging (optional)

2.7.2

This visit will last approximately 1 h and occur at baseline and 12 months. Scanning will be performed on a 3T Siemens Skyra scanner using a 20‐channel head coil. A T1‐weighted structural scan will be completed using 3D multi echo MPRAGE (MEMPRAGE) with real‐time motion correction and selective reacquisition^36^ (repetition time/inversion time/echo time [TR/TI/TE] = 2500/1300/1.79,3.65,5,51,7.37 ms, flip angle = 7°, field of view [FOV] = 256, matrix = 256 × 256 × 176, resolution = 1 mm^3^, scan time = 6.5 min). Volumetric analysis will be performed using segmentation and brain region parcellation pipelines implemented in FreeSurfer.^37^, ^38^ Regions of interest will include white matter, total gray matter, total intercranial volume, and hippocampal volume. To explore how the diet intervention impacts nutrient concentrations in the brain, brain glutathione (GSH)^39^ and vitamin C^40^ scans will be performed in an axial slice covering frontal and parietal regions using the doubly‐selective multiple quantum (MQ) CSI sequences with real‐time motion/shim correction (TE/TR = 115/1750 ms for GSH, TE/TR = 124/1750 ms for vitamin C, FOV = 20 cm, matrix = 10 × 10, slice thickness = 2.5 cm, scan time = 11.5 min each). Previous research in cognitively normal older adults suggest dietary interventions can lead to significant changes in GSH levels in as little as 12 weeks.^41^ Brain antioxidant signals will be quantified using the internal concentration reference method utilizing unsuppressed brain water signals. We will use previously established quantification procedures using in‐house data processing program written in Interactive Data Language (IDL; L3Harris, Bloomfield, CO, USA).^39^ Brain GSH and vitamin C concentrations in each voxel will be corrected for partial volume effect due to brain atrophy using effective tissue volume fraction calculated from magnetization‐prepared rapid gradient echo (MPRAGE) magnetic resonance imaging (MRI).^42^ We will use all the voxels that pass the preset criteria for spectral quality and tissue volume fraction in both region‐of‐interest analysis^39^ and voxel‐based analysis. We will also determine antioxidant concentrations in gray and white matter using well‐established regression‐based methods^42^ to examine potential differences of antioxidant concentrations in gray and white matter, and differential changes in gray matter and white matter after intervention.

#### Exit interview

2.7.3

At the completion of the 12‐month intervention, we will conduct structured interviews by Zoom with a 20% random sample of participants and study partners from each intervention arm to gather information that might be useful for improving the intervention. Qualitative content analysis (ATLAS.ti 6.2) will be conducted to search for broad themes across interviews.

#### Process measures

2.7.4

Attendance at education/behavioral counseling sessions will be obtained from interventionist records and expressed as the percentage of possible sessions attended, and compliance with self‐monitoring of diet (weight loss arm only) will be assessed as the percentage of prescribed monitoring days completed across 12 months.

### Incentives

2.8

Participants will receive $5.00 for each monthly session attended (up to $60 total) and will be allowed to keep the iPad and wireless scale (weight loss group only) upon study completion. Additionally, to compensate for time and travel, participants will receive $100 for completion of the outcome assessments at baseline, 6 and 12 months ($300 total for all three testing time points).

### Analysis/sample size

2.9

#### Sample size

2.9.1

The primary aim is to estimate the effect of a 12‐month weight loss intervention relative to control to determine if the intervention impacts relevant outcome variables, and if so, to precisely quantify the observed effect. The sample size was estimated using simulation with regard to plasma NfL based on the observation that changes in this biomarker is an early marker of AD in adults with DS.^2^ A recent 2021 paper reported an annual change in NfL of 3% in asymptomatic non‐progressive AD patients.^43^ Thus, we simulated annual data at baseline, 6 and 12 months assuming an average 3% annual increase in NfL for all participants in the control arm and an average change of 1.35% in the intervention arm which corresponds to a “small” Cohen's h effect size of 0.12. We modeled the between arm difference in NfL using a linear mixed model with a random intercept for each participant; with a sample size of 81 (*n* = 54 intervention; *n* = 27 control) and an estimated attrition rate of 20%. With these assumptions, we will be able to estimate the precision of the difference in the annualized increase in NfL with a 95% confidence interval of width 3%. Similar mixed models will be fit for all seven outcome variable categories to estimate the effects across all the domains of interest. A major concern with using estimated effects from pilot studies to power larger trials is that they are highly variable. This sample size and approach will guarantee good precision for our estimates which is especially important considering that there are currently no data regarding clinically relevant changes to use for powering a larger trial.

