Design and methodologic strengths of this trial include (1) randomized design with 2:1 allocation to intervention arms with assignments concealed until the initiation of the intervention; (2) adequate sample size to provide stable estimates of effect sizes per our primary aim; (3) strategies to ensure that we meet our participant recruitment goals; (4) retention/incentive strategies to reduce loss to follow‐up; (5) utilization of cognitive measures, and plasma biomarkers that are being used in the Alzheimer Biomarker Consortium for Down Sydnrome,^30^ the largest US cohort of adults with DS examining biomarkers related to AD, allowing for harmonization of data; (6) the use of a evidenced‐based intervention delivered by trained interventionists; (7) delivery of both intervention arms by the same interventionists to minimize interventionist effects; (8) procedures to ensure intervention fidelity; (9) assessments completed by trained research assistants blinded to intervention arm; (10) evaluation of staff inter‐rater reliability for all physical assessments; (11) the use of a novel technique for the assessment of dietary intake and quality; (12) exit interviews to obtain potentially useful information for improving the intervention; (13) an analysis plan to adequately address study aims. However, the study is not without limitations. Given the exploratory nature of the study not all outcomes will have adequate power for detecting difference between groups, and the 12‐month intervention length may not be long enough to detect changes in AD pathology.

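### Cohen's h is misapplied to percent change in NfL, so the small label is uninformative, and a 3-point interval does not support the promise of guaranteed good precision

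*Protocol article*

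**What the plan says.** Section 2.9.1 bases the sample size on a simulation of plasma NfL at three visits (study entry, month 6 and month 12). The control-arm input is stated as "assuming an average 3% annual increase in NfL for all participants in the control arm". For the treated participants the simulation takes "an average change of 1.35% in the intervention arm". The section equates this contrast with a small "Cohen's h effect size of 0.12". The model is a linear mixed model with a random intercept, fitted "with a sample size of 81", split 54 to 27 in favour of the intervention. Losses are allowed for through "an estimated attrition rate of 20"%. The result given is that the trial can estimate "the difference in the annualized increase in NfL with a 95% confidence interval of width 3"%.

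The section next says that similar models will be fitted for all seven outcome categories. It warns that effects estimated in pilot studies vary widely, and concludes: "This sample size and approach will guarantee good precision for our estimates". The Discussion repeats the assurance among the trial's strengths: "adequate sample size to provide stable estimates of effect sizes per our primary aim".

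**The concern.** Two things are wrong as written.

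First, Cohen's h is a distance between two proportions. The 3% and 1.35% are mean changes of a continuous measurement, not event rates. A standardised effect for such an outcome needs a standard deviation, and h has none. It would not even be defined if NfL fell in one arm, which is a possible result.

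Second, the precision is described as guaranteed, yet the stated interval is wider than the effect it is meant to quantify. It was derived for one biomarker, while the assurance is worded for the trial's estimates in general.

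Effect sizes are the declared product of Aims 1 and 2 (Table 1), and the article says they are to inform a larger trial. This section is also the only justification given for 81 participants. A reader who takes the small label or the guarantee at face value gets a wrong picture of what the trial can deliver.

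**Working it through.** **Inputs, all from section 2.9.1.** Annual change 3% and 1.35%, difference 3 − 1.35 = 1.65 points; allocation 54/27; attrition 20%, leaving 43.2 and 21.6; 95% confidence interval (z = 1.96) of width 3 points. The article gives no SD for NfL change.

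**1. Reproduce the stated effect size.** h = 2·asin(√0.03) − 2·asin(√0.0135) = 0.115, which rounds to the stated 0.12. The figure is therefore correct as an h. It was obtained by treating the two percent changes as proportions.

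**2. SD implied by the stated width.** Width = 2 × 1.96 × SD × √(1/n₁ + 1/n₂).
- SE = 3/(2 × 1.96) = 0.765
- √(1/43.2 + 1/21.6) = 0.2635
- SD of annual change = 0.765/0.2635 = 2.90 points
- Standardised difference in change = 1.65/2.90 = 0.57

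**3. Other readings of the same sentence.**

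| Reading | Implied SD | 1.65/SD |
|---|---|---|
| Full width 3, 20% attrition | 2.90 | 0.57 |
| Full width 3, all 81 analysed | 3.25 | 0.51 |
| Half-width 3, 20% attrition | 5.81 | 0.28 |

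**4. Check against the planned visit structure.** With visits at 0, 6 and 12 months, the SD of a participant's fitted annual slope is √2 times the residual SD, so 2.90 corresponds to a residual SD of 2.90/√2 = 2.05. A simulation of the three-visit slope comparison used a within-person estimator and an assumed dropout pattern (10% lost after baseline, a further 10% after 6 months). With residual SD 2.05 it gave a mean width of 2.95, in line with step 2.

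**5. What a 3-point width means for the assumed effect.**
- Interval centred on 1.65: 1.65 ± 1.5 = 0.15 to 3.15
- Width relative to the effect: 3/1.65 = 1.8
- Limits relative to the control-arm rise of 3: 0.15/3 = 5% and 3.15/3 = 105%

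So even if the simulation is right and the result falls exactly on its assumption, the interval covers everything from almost no slowing of the NfL rise to slightly more than complete prevention of it.

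**6. Dependence on the SD** (illustrative values, 43.2/21.6 analysed). SD 2 gives width 2.1; SD 2.9 gives 3.0; SD 5 gives 5.2; SD 10 gives 10.3. The width is proportional to an SD that the sample size alone does not control.

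**The case against.** The tempting stronger reading is that the two figures contradict each other: if the standardised effect were 0.12, the SD of change would be 1.65/0.12 = 13.75 and the interval about 14.2 points wide, not 3. The document does not support that reading, for three reasons.

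- The 0.12 is stated as an h, and as an h it is numerically correct. It is on a different scale from a standardised mean difference. An index that contains no variability cannot conflict with an interval width.
- Even if 0.12 is read as a standardised difference, the 14-point width follows only when the SD of change is the denominator. With assumed values of 13.75 for the between-person SD of the level and 2.05 for the residual SD (intraclass correlation 1 − 2.05²/13.75² = 0.978), 1.65/13.75 = 0.12, while the random intercept removes the stable differences and the slope interval is still about 3 points wide.
- The 3% width came from a simulation and is attainable if the SD of annual change is about 2.9. That SD may be in the full protocol, so its absence from a condensed article is not a fault.

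It is also fair to say that the article sets no precision threshold, tests no hypotheses in the between-arm analysis (so power is not the yardstick), and admits that not all outcomes will be adequately powered. The sentence on seven outcome categories promises similar models, not a 3% width for each.

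All of this stands. It does not make h a valid index for NfL change, and it does not support the word guarantee. The admission about power does not withdraw the claim of stable effect sizes, which is listed as a strength in the same paragraph.

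**Conclusion.** The point holds in this limited form. The effect-size label is invalid for the outcome: h = 0.12 says nothing about the standardised NfL effect. The article's own precision figure implies a standardised difference in change of about 0.57 (0.51 without attrition, 0.28 if 3% is a half-width). These values assume a simple two-group comparison of annual change, with the SD back-solved from the stated width.

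The 3% width is neither confirmed nor refuted. Taken as given, it is 1.8 times the assumed effect and spans 5% to 105% of the control-arm rise, so neither guaranteed good precision nor stable effect sizes follows from it. The general wording is weaker still for other outcomes: no width is stated for them, and the neuroimaging visit is optional, so those estimates may rest on fewer people. This is a fault in how the sample size is justified and described. It does not show that 81 is the wrong number.

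**What to change.** - In section 2.9.1, delete Cohen's h and the word small. Give the assumed effect as 1.65 percentage points per year and as 1.65 divided by the SD of annual change used in the simulation, and state that SD.
- Replace the guarantee in section 2.9.1, and the stable-estimates wording in the Discussion, with the expected interval width set against the 1.65-point effect. Say whether 3% is a full width or a half-width.
- Limit the precision statement to NfL.

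The cost is rewording plus reporting an input that the simulation must already contain. Neither the sample size nor the analysis changes. The stated precision will read less favourably.
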